**Figure 1 fig1:**
[figure not shown]
Flow diagram. ACT, actigraphy; AES, Acupuncture Expectancy Scale; BHWSS, Benzodiazepine Hypnotics Withdrawal Symptom Scale; CSD, Consensus Sleep Diary; ESS, Epworth Sleepiness Scale; FSS, Fatigue Severity Scale; GAD-7, Generalized Anxiety Disorder 7-item; ISI, Insomnia Severity Index; NBZDs, Non-Benzodiazepines; PHQ-9, Patient Health Questionaire-9; PSG, polysomnography; PSQI, Pittsburgh Sleep Quality Index; VAS, Visual Analogue Scale; 5-HT: 5-hydroxytryptamine.

**Table 1 tab1:** Trial processes chart.

Week	0	1	2	3	4	5	6	7	8	9	10
	Baseline	Treatment phase						Follow-up phase			
Patients											
Enrolment	**×**										
Sign informed consent	**×**										
General information	**×**										
Medication diary	**×**	**×**	**×**	**×**	**×**	**×**	**×**	**×**	**×**	**×**	**×**
PSG	**×**						**×**				
ACT	**×**						**×**				
Groups											
Acupuncture group		18 treatments									
Sham- acupuncture group		18 treatments									
Outcome measurement											
Successful drug discontinuation rate							**×**				
CSD	**×**		**×**		**×**		**×**		**×**		**×**
ISI	**×**		**×**		**×**		**×**		**×**		**×**
PSQI	**×**						**×**				**×**
ESS	**×**						**×**				**×**
FSS	**×**						**×**				**×**
GAD-7	**×**						**×**				**×**
PHQ-9	**×**						**×**				**×**
NBZDs reduction rate	**×**		**×**		**×**		**×**		**×**		**×**
BHWSS			**×**		**×**		**×**		**×**		**×**
VAS	**×**		**×**		**×**		**×**		**×**		**×**
AES	**×**										
Blinding assessment		**×**		**×**			**×**				
Adverse events											
Reasons for dropouts or withdrawals	**×**	**×**	**×**	**×**	**×**	**×**	**×**	**×**	**×**	**×**	**×**

ACT, actigraphy; AES, Acupuncture Expectancy Scale; BHWSS, Benzodiazepine Hypnotics Withdrawal Symptom Scale; CSD, Consensus Sleep Diary; ESS, Epworth Sleepiness Scale; FSS, Fatigue Severity Scale; GAD-7, Generalized Anxiety Disorder 7-item; ISI, Insomnia Severity Index; NBZDs, non-benzodiazepines; PHQ-9, Patient Health Questionaire-9; PSG, polysomnography; PSQI, Pittsburgh Sleep Quality Index; VAS, Visual Analogue Scale; 5-HT, 5-hydroxytryptamine.

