### Withdrawal criteria

Participants will be withdrawn from the study if any of the following occur:

(1) Participants who develop intolerable severe withdrawal symptoms during the NBZDs tapering process.(2) Voluntary withdrawal at the participant’s request.(3) Withdrawal of informed consent.(4) Emergence of exclusion criteria during the study period.(5) Poor treatment compliance, defined as attendance at fewer than 50% of scheduled acupuncture sessions.(6) Occurrence of adverse events that preclude continued participation or pose a risk to participant safety.

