#### Secondary outcome measures

Secondary outcomes are assessed at baseline, during treatment, and during follow-up. Detailed assessment procedures are provided in the Supplementary Appendix S1; assessment time points are summarized in Table 1.

(1) *Subjective Sleep Scales*

① Consensus Sleep Diary (CSD): Records total sleep time (TST), sleep onset latency (SOL), wake after sleep onset (WASO), sleep efficiency (SE), subjective sleep quality, and medication use (32–35).

② Insomnia Severity Index (ISI): 7-item scale (0–28) (36); scores ≥15 indicate clinically significant insomnia (37); a reduction of ≥8 points indicates meaningful improvement (38).

③ Pittsburgh Sleep Quality Index (PSQI): Global sleep quality (0–21); scores > 5 indicate poor sleep quality (39–42).

(2) *Daytime Functioning Assessment*

① Epworth Sleepiness Scale (ESS): Daytime sleepiness across eight situations (43, 44).

② Fatigue Severity Scale (FSS): 9-item scale (9–63); scores ≥36 indicate clinically significant fatigue (45–47).

③ Generalized Anxiety Disorder 7-item Scale (GAD-7): Anxiety severity (0–21) (48–50).

④ Patient Health Questionnaire-9 (PHQ-9): Depression symptom severity (51, 52).

(3) *Medication Reduction Response Assessment*

① NBZDs Reduction Rate

The NBZDs reduction rate was calculated using the following formula: NBZDs reduction rate = (Pre-treatment weekly NBZDs dose - Post-treatment weekly NBZDs dose) / Pre-treatment weekly NBZDs dose * 100% (Note: Pre-treatment refers to the baseline period, and post-treatment refers to week 6 of the treatment period) (16).

② Benzodiazepine Hypnotics Withdrawal Symptom Scale (BHWSS): 12-item self-report (3-point scale) assessing withdrawal symptoms (53, 54).

③ Medication Craving Visual Analogue Scale (VAS): 0–10 scale (0 = no craving, 10 = extreme craving) (55).

(4) *Objective sleep assessment parameters*

① Polysomnography (PSG): performed as the primary objective sleep assessment, with all participants undergoing one night of 8-h monitoring during screening to exclude other sleep disorders; sleep stages and parameters were manually scored according to the AASM Manual (Version 3.0) (56–58).

② Actigraph (ACT): Recorded for 7 consecutive days at baseline and at the end of intervention; parameters included number of awakenings (NOA), total wake time (TWT), sleep onset latency (SOL), total sleep time (TST), and sleep efficiency (SE) (59–62).

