### Efficacy evaluation criteria

① Primary Efficacy Outcome Measures

The primary efficacy outcome is the successful discontinuation rate of NBZDs at the end of the 6-week treatment period. Between-group differences in discontinuation rate will be evaluated using regression-based methods appropriate for binary outcomes.

② Secondary Efficacy Outcome Measures

a. Subjective Sleep Efficacy Evaluation

Subjective sleep outcomes, including the Insomnia Severity Index (ISI) and Pittsburgh Sleep Quality Index (PSQI), will be analyzed using longitudinal mixed-effects models incorporating repeated measurements across predefined study time points to estimate treatment effects over time.

b. Objective Sleep Efficacy Assessment

Objective sleep parameters derived from PSG and ACT will be analyzed using longitudinal mixed-effects models to account for within-subject correlation and to evaluate changes across study time points.

c. Daytime Functioning Assessment

Daytime functioning outcomes will be analyzed using longitudinal mixed-effects models to assess treatment effects across time.

d. NBZDs Reduction Response Evaluation

Medication reduction responses, including NBZDs reduction rate, withdrawal symptoms, and craving scores, will be evaluated using regression-based models appropriate to outcome type, with longitudinal modeling applied where repeated measurements are available.

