### Statistical analysis

All statistical analyses will be conducted using SPSS version 28.0 (IBM Corp., Armonk, NY, United States) according to the intention-to-treat principle. A two-sided *p* < 0.05 will be considered statistically significant.

Continuous variables will be summarized as mean ± standard deviation or median (interquartile range), as appropriate. Categorical variables will be presented as frequencies and percentages. Between-group differences at single time points will be assessed using independent-samples *t*-tests or Mann–Whitney U tests for continuous variables and *χ*^2^ or Fisher’s exact tests for categorical variables.

Longitudinal outcomes will be analyzed using linear mixed-effects models with fixed effects for group, time, and group-by-time interaction, and random intercepts for participants. Missing data will be handled using likelihood-based estimation under the missing-at-random assumption. Multiple imputation will be conducted as a sensitivity analysis.

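### Seven secondary measures have no value between baseline and week 6, so the stated mixed models take only baseline from early leavers and ignore the week-2 and week-4 symptom scores linked to withdrawal

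*Protocol article*

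**What the plan says.** The Statistical analysis section specifies "linear mixed-effects models with fixed effects for group, time, and group-by-time interaction, and random intercepts for participants". It then states: "Missing data will be handled using likelihood-based estimation under the missing-at-random assumption", and adds: "Multiple imputation will be conducted as a sensitivity analysis". The variables of the imputation model are not given.

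Efficacy evaluation criteria applies mixed models to each group of outcomes. Item b reads: "Objective sleep parameters derived from PSG and ACT will be analyzed using longitudinal mixed-effects models". Item c reads: "Daytime functioning outcomes will be analyzed using longitudinal mixed-effects models to assess treatment effects across time". Item a does the same for PSQI.

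Table 1 ("Trial processes chart") gives the visits:

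- PSG and actigraphy: weeks 0 and 6. Secondary outcome measures agrees for actigraphy ("Recorded for 7 consecutive days at baseline and at the end of intervention"), and the text after it says that neither is repeated at the week-10 follow-up.
- PSQI, ESS, FSS, GAD-7 and PHQ-9: weeks 0, 6 and 10.
- ISI, sleep diary, craving VAS and NBZDs reduction rate: weeks 0, 2, 4, 6, 8 and 10. BHWSS is the same without week 0.

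The first ground for withdrawal from the study is "Participants who develop intolerable severe withdrawal symptoms during the NBZDs tapering process". The Sample size section allows for 20% dropout overall and gives no figure by arm.

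**The concern.** A likelihood-based mixed model under missing at random protects against dropout only through the data that enter the model. For ISI, the values at weeks 2 and 4 are in the model, so dropout that follows a poor week-4 score is largely accounted for. For the seven sparse measures nothing lies between baseline and week 6. Someone who leaves in weeks 1 to 5 can still be in the full analysis set through a week-2 ISI, yet adds only a baseline value to, say, the PSQI model.

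Criterion (1) links some of that dropout to symptoms which did not exist at baseline. If those symptoms also predict sleep, mood or fatigue at week 6, the participants who stay differ from those who leave in a way that baseline and arm cannot explain. Between-arm estimates are then biased whenever this selection differs between arms. These seven measures carry all the objective-sleep and daytime-function evidence of the trial, and the symptom scores that would make the assumption more credible are already collected.

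**Working it through.** **1. What the plan supplies.** It gives no figure for this bias. The relevant inputs are 39 per arm and 20% dropout, so 39 × 0.20 = 7.8 leavers and 39 × 0.80 = 31.2 completers per arm.

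**2. Assumptions not in the documents.** Each outcome has SD 1. The correlation of baseline with later values is 0.4. The correlation of the week-2/4 symptom score with the week-6 outcome is 0.7, with 0.5 and 0.3 as alternatives. The true effect is −0.50 SD on both the symptom score and the outcome (negative means benefit). Dropout is logistic in the symptom score, with slope 1 per SD unless stated.

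**3. Estimators, per arm.**

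- Baseline only: mean(Y6 among completers) − b × [mean(Y0 among completers) − mean(Y0 among all)], where b is the completers' slope of Y6 on Y0.
- With auxiliary: the same, with the symptom score added to the regression and averaged over all participants.

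The treatment effect is the difference between arms. A random-intercept version that contrasts change from baseline agreed with the baseline-only estimator to within 0.01.

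**4. Large-sample results** (300,000 to 400,000 per arm, Monte Carlo error about 0.003). Entries are the baseline-only estimate of a true −0.50, by symptom–outcome correlation.

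| Dropout, EA / sham | 0.7 | 0.5 | 0.3 |
|---|---|---|---|
| 10% / 30% | −0.42 | −0.44 | −0.48 |
| 15% / 25% | −0.46 | −0.47 | −0.49 |
| 20% / 20% | −0.50 | −0.50 | −0.49 |
| 25% / 15% | −0.54 | −0.53 | −0.51 |
| 30% / 10% | −0.59 | −0.55 | −0.52 |
| 20% / 20%, symptom-driven in sham only | −0.41 | −0.44 | −0.47 |
| 20% / 20%, symptom-driven in EA only | −0.60 | −0.56 | −0.52 |
| One rule for both arms, slope 0.5 (18% / 22%) | −0.49 | −0.49 | −0.50 |
| One rule for both arms, slope 1 (17% / 23%) | −0.47 | −0.48 | −0.49 |
| One rule for both arms, slope 2 (15% / 25%) | −0.43 | −0.46 | −0.48 |

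Adding the symptom score gave −0.49 to −0.51 throughout. With no true effect and the same rule and rates in both arms, the baseline-only estimate showed no bias.

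**5. At 39 per arm.** The baseline-only bias was again 0 to 0.10 SD, mostly 0.01 to 0.05 outside the extreme patterns. The auxiliary removed most of it. Root mean squared error was similar:

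- correlation 0.7: 0.25–0.26 baseline only, 0.24–0.25 with the auxiliary;
- correlation 0.3: 0.25 baseline only, 0.25–0.26 with the auxiliary.

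**6. Scale.** The standard error with 31 completers per arm is about √(2/31) × √(1 − 0.4²) = 0.254 × 0.917 = 0.23 SD. The largest bias, 0.10, is 0.10 / 0.23 = 0.43 of a standard error.

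**The case against.** A likelihood-based mixed model under missing at random is a standard main analysis, and auxiliary variables for secondary outcomes are often left to a SAP. Multiple imputation is already planned and may use the week-2/4 scores. This stands in part: the missing list of imputation variables is not in itself a fault. But the article does fix the main model and its assumption, and that model cannot use the intermediate scores whatever a SAP adds to the sensitivity analysis.

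The calculation also flatters both the problem and the remedy. It makes all dropout depend on the symptom score and treats that score as known for every leaver. Only one of the six withdrawal grounds is intolerable withdrawal symptoms, and the tapering protocol first reverts the dose and tries again. Those who leave before week 2 have no intermediate score. All of this stands, and it is why the size is put as modest.

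A reader might infer that the plan biases these results towards no effect. The documents do not support that, because they give no dropout by arm. The direction follows if electroacupuncture eases withdrawal, as the Discussion hypothesises, and both arms obey one rule; the opposite pattern inflates the effect. A reader might also infer that criterion (1) contradicts the missing-at-random statement. It makes the assumption hard to defend given baseline and arm, but the two texts do not conflict. Finally, a participant who misses only week 6 can still supply week 10 for the five questionnaires, so the baseline-only problem concerns those withdrawn before week 6.

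**Conclusion.** The point holds for seven secondary measures. For anyone withdrawn before week 6 the stated models have only a baseline value, while withdrawal is tied in part to symptoms measured at weeks 2 and 4 and left out. Under the stated assumptions the bias is about 0 to 0.10 SD on a true 0.50 SD. It is 0.01 to 0.07 SD (2% to 14%) towards no effect at correlation 0.7 if one dropout rule applies to both arms and electroacupuncture works. It shrinks further when the symptom score is only weakly related to the outcome, which may be so for PSG and actigraphy. Shrinkage well beyond this needs near-deterministic dropout together with strong correlations and a large early benefit, and nothing in the documents supports that combination. The sign depends on which arm loses more symptomatic participants. The primary outcome is unaffected. The change is worth making because it is cheap and reduces bias in either direction; it should not be expected to improve precision.

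**What to change.** For PSG, actigraphy, PSQI, ESS, FSS, GAD-7 and PHQ-9, state that the multiple imputation already planned uses the outcome's baseline value, arm, and a compact set of auxiliaries: the last available week-2/4 ISI and BHWSS. A joint model of each outcome with the two-weekly ISI would serve as well. Report the result next to the mixed model, and say in advance that the conclusion rests on the auxiliary-informed estimate if the two differ materially.

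The auxiliary set should stay small. Imputing by arm from baseline plus two visits each of ISI, BHWSS, VAS and dose would mean 1 + 4 × 2 = 9 predictors on about 31 completers per arm, which is too many to fit reliably.

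The cost is analysis wording and some programming, with no new data. The drawbacks are slightly larger variance where the auxiliaries are weakly related to the outcome, and little help for those who leave before week 2. Reporting dropout by arm and reason would show readers which way any remaining bias is likely to run.

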## Discussion

This randomized, controlled, single-blind trial is designed to evaluate the efficacy and safety of electroacupuncture as an adjunctive intervention to facilitate tapering of NBZDs in patients with CID. The present discussion contextualizes the scientific rationale for the study, outlines the anticipated clinical implications of the findings, and critically appraises key methodological considerations.

### Clinical management of chronic insomnia

Cognitive behavioral therapy for insomnia (CBT-I) is internationally recognized as the first-line treatment for CID. This multimodal intervention encompasses sleep restriction, stimulus control, relaxation training, sleep hygiene education, and cognitive restructuring (67), and has demonstrated efficacy not only in alleviating insomnia symptoms but also in modifying maladaptive sleep-related cognitions and behaviors, thereby promoting durable improvements in sleep regulation (68). However, the implementation of CBT-I in China remains limited due to multiple barriers, including high treatment costs, insufficient availability of trained providers, and the relatively prolonged treatment course (69).

The high prevalence of CID and the widespread reliance on NBZDs, together with the well-documented challenges associated with their long-term use, create a substantial clinical dilemma. Although NBZDs remain a cornerstone of pharmacological management, their dependence potential and withdrawal-related distress constitute major barriers to discontinuation, leaving many patients trapped in a cycle of chronic use. Existing discontinuation strategies—including pharmacological substitution, which carries its own adverse effect profile (12, 13, 15), and educational or behavioral interventions with variable implementation fidelity—have not consistently provided safe and effective solutions (70, 71). This trial addresses this unmet clinical need by evaluating electroacupuncture as a non-pharmacological adjunct to support medication deprescribing. By focusing specifically on NBZDs users, the study targets the most widely prescribed first-line hypnotics, thereby enhancing the direct clinical relevance of its findings.

### The role of acupuncture in tapering NBZDs

The current evidence base regarding acupuncture-assisted medication discontinuation remains limited and heterogeneous. Conflicting findings from prior randomized controlled trials, including the negative results reported by Lao et al. (21) and the positive outcomes described by Zhang et al. (24) underscore the need for methodologically rigorous investigation. The present trial incorporates several design refinements intended to address key limitations of previous studies and provide more definitive evidence.

First, the lack of stratification by benzodiazepine receptor agonist subtype may have confounded prior findings. Although traditional benzodiazepines and NBZDs share overlapping pharmacodynamic properties, they differ in pharmacokinetic profiles and receptor subunit selectivity, factors that may influence withdrawal severity and discontinuation success (72). By restricting enrollment to NBZDs users, the present study enhances population homogeneity, reduces clinical heterogeneity, and increases statistical sensitivity to detect treatment-specific effects.

Second, the challenge of maintaining adequate blinding in acupuncture research is addressed through a rigorous sham-control procedure. The use of validated non-penetrating needles applied at the same acupoints is intended to preserve participant blinding while controlling for non-specific effects associated with needling procedures, including expectancy, attention, and therapeutic context. This design strengthens internal validity and facilitates a more precise evaluation of the specific physiological effects of electroacupuncture.

### Potential mechanisms of acupuncture in tapering NBZDs

The potential therapeutic effects of electroacupuncture in facilitating NBZDs tapering may be considered within converging neurobiological and theoretical frameworks. From a neurobiological perspective, chronic NBZDs exposure induces adaptive changes in the *γ*-aminobutyric acid (GABA)ergic system, including downregulation of GABA_A receptors. Withdrawal disrupts neurochemical equilibrium, producing central nervous system hyperexcitability that manifests as rebound insomnia, anxiety, and other withdrawal symptoms, which in turn increase relapse risk (5, 9). Electroacupuncture has been suggested by some preclinical and clinical studies to potentially modulate central neurotransmitter systems, possibly including promoting GABA synthesis and release, and influencing other systems involved in sleep and arousal, such as the monoaminergic and orexin systems (20, 73). It is hypothesized that by restoring neurochemical homeostasis, electroacupuncture could “bridge” the neuroadaptive gap during NBZDs taper, mitigating withdrawal symptoms and stabilizing sleep architecture, thereby might enabling successful dose reduction.

From the perspective of traditional Chinese medicine (TCM), long-term NBZDs use is conceptualized as disrupting the harmonious flow of Qi and Blood, contributing to Liver Qi stagnation transforming into Fire that disturbs the Heart and destabilizes the Shen (mind-spirit). The resulting internal disequilibrium is considered within TCM theory as a central mechanism underlying persistent insomnia and anxiety during medication withdrawal. The selected partial acupoint prescription—including Hegu (LI4), Taichong (LR3), Neiguan (PC6), Shenmen (HT7), Sanyinjiao (SP6), Baihui (GV20), Sishencong (EX-HN1), Anmian (Extra)—is intended to soothe the Liver, clear pathogenic Fire, nourish the Heart, and calm the Shen. This integrative framework, combining hypothetical neurobiological modulation with TCM-based regulatory principles, provides a potential coherent theoretical rationale for the intervention.

Importantly, the current study was not designed to test any neurobiological or TCM-based mechanisms. All mechanistic interpretations presented above are hypothetical and exploratory in nature, based solely on literature-derived inferences rather than direct experimental evidence from this trial. We did not measure any biomarkers (e.g., GABA, cortisol, or cytokines) nor employ neuroimaging (e.g., fMRI). Future studies incorporating biomarker panels and neuroimaging endpoints are necessary to validate or refute these proposed mechanisms and to identify patient subgroups most likely to benefit from electroacupuncture-assisted NBZDs tapering.

### Potential impact and clinical implications

If electroacupuncture demonstrates efficacy in facilitating NBZDs discontinuation, the findings would have important implications for the management of CID. Electroacupuncture could be incorporated into structured deprescribing programs as a safe, non-pharmacological adjunct, offering a therapeutic option for patients who have failed prior discontinuation attempts, are intolerant to pharmacological alternatives, or prefer non-drug interventions. Successful reduction of NBZDs dependence may also contribute to decreased risks associated with long-term hypnotic use, including falls, cognitive impairment, and healthcare utilization (6, 7).

Conversely, if no significant benefit is observed despite methodological enhancements, the results would provide important negative evidence. Such findings would suggest that previously reported benefits may reflect non-specific effects or that acupuncture alone may be insufficient to overcome neuroadaptive changes associated with NBZDs dependence. This outcome would help refine future research directions and guide the development of alternative or combination-based non-pharmacological strategies.

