Objective sleep measures (PSG and ACT) were not collected at the 10-week follow-up because the primary focus of this trial was NBZDs discontinuation, not direct sleep improvement. To enhance patient convenience and retention, some participants will be followed up online (video/phone) at week 10, precluding in-person objective measurements. PSG is resource-intensive and burdensome, and actigraphy requires prolonged device wear, both of which could increase dropout rates in this pragmatic feasibility study.

(5) *Assessment of acupuncture treatment expectancy*

The Acupuncture Expectancy Scale (AES) is a four-item instrument rated on a 5-point Likert scale, yielding total scores ranging from 4 to 20 (63). The AES evaluates participants’ pretreatment expectations regarding acupuncture intervention, with higher scores indicating greater expectancy. Scores >12 indicate high expectancy, whereas scores ≤12 indicate low expectancy (64). The AES was administered once prior to treatment initiation.

(6) *Blinding assessment*

Blinding effectiveness will be evaluated by asking participants whether they perceived needle penetration during treatment. Assessments will be conducted at three time points: baseline (after the first treatment session), mid-term (end of week 3), and final (end of week 6, after the last treatment session). Participants will also be asked to guess their group assignment (electroacupuncture, sham, or unsure) and to rate their confidence level. The blinding index will be calculated at each time point. If systematic unblinding is detected, sensitivity analyses will be performed excluding participants who correctly guessed their assignment with high confidence.

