### Sample size

The expected discontinuation efficacy rate for the sham acupuncture group in the sample size calculation was derived from a randomized controlled trial that enrolled 144 long-term benzodiazepine users (21). However, this trial yielded a negative result, which might be attributable to the simultaneous inclusion of both BZDs and NBZDs in the study medication (22). Therefore, only the sham acupuncture group discontinuation rate of 10.83% was adopted from that trial, while the expected successful discontinuation rate for the acupuncture group was based on our pilot study.

A pilot study was conducted at our center prior to the main trial to assess the feasibility of the intervention and to obtain preliminary estimates of effect size. Ten eligible patients with chronic insomnia disorder who had used NBZDs regularly for >6 months received electroacupuncture (three times per week for 6 weeks) combined with the standardized 6-week NBZD tapering protocol (25% dose reduction every week). The successful discontinuation rate was 50.00% (5/10). No serious adverse events were reported. Detailed pilot study results are provided in Supplementary Appendix S2.

Based on expected outcomes and relevant published literature (21), this study hypothesized that after treatment, the discontinuation efficacy rates of NBZDs at 6-week post-treatment for the electroacupuncture group and sham needle and sham electroacupuncture group would be 50.00 and 10.83%, respectively. This study set *α* = 0.05 and 1-*β* = 0.90, employing a two-sided test with equal sample sizes between treatment and control groups. Referencing the sample size estimation formula for comparing efficacy rates between two groups from Sun Zhenqiu’s Medical Statistics, the calculation formula was as follows:

$$n=1641.4/{\left[\frac{\left(u_{\alpha }+u_{\beta }\right)}{\sin^{-1}\sqrt{P_{1}}-\sin^{-1}\sqrt{P_{2}}}\right]}^{2}$$

where 
$u_{\alpha }$
=1.96 (for 
α
=0.05, two-sided), 
$u_{\beta }$
=1.282 (for 
β
=0.10), P_1_ = 50.00%, and P_2_ = 10.83%. The calculation yields n = 31.7 ≈ 32 cases. Accounting for dropout rates, the clinically set dropout rate is 20%, resulting in a final sample size of 39 participants per group, totaling 78 participants across both groups.

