### Study limitations

Several limitations should be acknowledged. First, the generalizability of our findings may be constrained by the single-center design and the use of a standardized tapering protocol. As an early-stage exploratory study, the single-center design was intentionally adopted to maximize internal validity, minimize the heterogeneity and costs associated with multi-center trials, and enhance reproducibility, thereby laying the groundwork for future multi-center investigations. However, this design inevitably involved a relatively homogeneous and highly adherent patient population, which may introduce selection bias. Additionally, access to specialized acupuncturists and frequent monitoring—resources that are not universally available in routine clinical settings—further limits the applicability of our findings. Furthermore, while the standardized tapering protocol reduced performance bias, improved reproducibility, and provided a clear estimate of treatment efficacy, its rigidity may lead to suboptimal adherence in some patients and fails to account for real-world interpatient variability. Therefore, our results reflect efficacy under optimized conditions; the effectiveness of this intervention in heterogeneous, resource-limited, or less supervised settings may differ. Future pragmatic multi-center trials incorporating flexible, patient-centered tapering strategies are needed to establish broader applicability. Second, the single-blind design ensures participant blinding but does not permit blinding of treating acupuncturists, introducing the possibility of performance bias. This design was selected to preserve treatment fidelity while maintaining methodological rigor. Third, it must be acknowledged that the small sample size of the pilot study may have introduced uncertainty in the estimation of the effect size. Therefore, after completion of the main trial, the pilot data will be pooled with the main trial data to conduct sensitivity analyses assessing the robustness of the conclusions under different effect size assumptions. Furthermore, future multi-center, large-sample confirmatory trials are recommended to validate the findings of the present study. As a final note, although plausible neurobiological mechanisms are proposed, mechanistic pathways are not directly evaluated. Future studies incorporating neuroimaging, electrophysiological measures, or biomarker assessments would help clarify the underlying mechanisms of action.

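### A non-significant result is to be read as negative evidence, but the trial has only about 40 to 60% power for a 20-point gain in discontinuation

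*Protocol article*

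**What the plan says.** The Discussion, under Potential impact and clinical implications, covers both outcomes of the trial. For the unfavourable one it states that "if no significant benefit is observed despite methodological enhancements, the results would provide important negative evidence". It adds, in hedged terms, that earlier positive reports might then be put down to non-specific effects, or that acupuncture by itself might not be enough. The condition is lack of significance. No confidence interval, margin or smallest worthwhile difference is attached to it there, or under Efficacy evaluation criteria, Sample size or Statistical analysis.

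The Sample size section assumes that discontinuation rates for electroacupuncture and sham "would be 50.00 and 10.83%, respectively", with two-sided alpha 0.05 and 90% power. The 50% is the result in ten pilot patients, all given electroacupuncture. The 10.83% is the sham rate of an earlier trial in long-term benzodiazepine users. "The calculation yields n = 31.7 ≈ 32 cases", raised to 39 per group for 20% dropout.

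Study limitations says: "As an early-stage exploratory study, the single-center design was intentionally adopted to maximize internal validity". It concedes that the small pilot leaves the effect size uncertain, and it recommends larger multi-centre trials.

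**The concern.** Non-significance counts against a treatment only to the extent that the trial would have detected the benefits that matter. This trial is powered for a very large effect taken from ten patients. If the true gain is smaller but still worth having, a non-significant result is a likely outcome, and the article has already said how it would be read. The earlier negative trial, which the article itself treats as hard to interpret, would be followed by a second null that is equally hard to interpret but labelled as evidence against the treatment.

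**Working it through.** **Inputs from the Sample size section.** Rates 0.5000 and 0.1083; two-sided alpha 0.05 (1.96); power 0.90 (1.282); 32 per group before dropout; 20% dropout; 39 per group. The planned difference is 50.00 - 10.83 = 39.17 points. If 20% are lost, 39 × 0.8 = 31.2, or about 31 per group. I use 39 and 31 as the two ends.

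**The plan's own figure.** With the mean rate p̄ = 0.30415, the usual two-proportion formula is

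n = [1.96√(2p̄(1-p̄)) + 1.282√(p₁(1-p₁) + p₂(1-p₂))]² / (p₁-p₂)² = (1.275 + 0.755)² / 0.3917² = 26.9.

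The continuity correction, (n/4)[1 + √(1 + 4/(n × 0.3917))]², gives 31.8, or 32, which agrees with the stated 32. Then 32 × 1.2 = 38.4, or 39. The arcsine expression exactly as printed gives 31.6; in its usual orientation it gives 25.9. That is a separate matter and does not change what follows.

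**Power for smaller gains.** I held sham at 10.83% and summed the exact binomial probabilities of all outcomes in which electroacupuncture is significantly better at two-sided 0.05. The pooled z test is the uncorrected chi-square test and also the score test of an unadjusted logistic model. Fisher's test is the other option named under Statistical analysis.

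| True gain | z, 39/arm | Fisher, 39/arm | z, 31/arm | Fisher, 31/arm |
|---|---|---|---|---|
| 15 points | 41% | 31% | 33% | 22% |
| 20 points | 60% | 50% | 50% | 38% |
| 25 points | 77% | 69% | 67% | 56% |
| 30 points | 89% | 83% | 80% | 72% |
| 39.17 points | 98% | 96% | 94% | 91% |

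Power of 80% is reached at about 26 points (z, 39 per arm), 29 (Fisher, 39), 30 (z, 31) and 33 (Fisher, 31).

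The complement is the chance of a non-significant result. It is 40 to 62% for a true 20-point gain, which would bring discontinuation from 10.83% to 30.83%, and 59 to 78% for a true 15-point gain.

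**An example of a null.** Take 12/39 against 5/39, that is 30.8% against 12.8%, a difference of 17.9 points.
- Pooled rate 17/78 = 0.218; standard error √(0.218 × 0.782 × 2/39) = 0.0935; z = 0.1795/0.0935 = 1.92; chi-square p = 0.055. Fisher p = 0.098.
- Wilson limits are 0.186 to 0.464 and 0.056 to 0.267. Newcombe lower limit: 0.1795 - √(0.122² + 0.139²) = -0.005. Upper limit: 0.1795 + √(0.157² + 0.072²) = 0.352.

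The interval of about -0.5 to +35 points includes no effect and also gains above 30 points. Under the stated reading this result would count as negative evidence.

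**The case against.** The strongest reply is that this is Discussion prose and not a decision rule. The inferences drawn from a null are hedged, and the article never says that a benefit would be shown to be absent. Study limitations admits the pilot's uncertainty, plans sensitivity analyses and asks for larger trials. The final report would be expected to give an interval in any case. Most of this stands as a description of the text. However, the label of negative evidence is not itself hedged, and nothing under Study limitations says that a null would be inconclusive.

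A reader might infer that the design can detect only differences near 39 points. The documents do not support that. The 39.17 points is the planning effect, and 80% power is reached well below it.

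A reader might also infer that a useful benefit would usually be declared absent. That goes too far, because the article names no useful benefit and its wording stops short of absence. At 39 per arm with the z test, a true 20-point gain would be significant more often than not.

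Finally, the article calls itself exploratory and, under Secondary outcome measures, a feasibility study ("both of which could increase dropout rates in this pragmatic feasibility study"), while hoping for more definitive evidence than earlier trials gave. These labels sit uneasily together, but this is a matter of wording that changes no result, and the point does not rest on it.

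The worked example was chosen just above the significance threshold. It shows that such a case can arise, not how often; the power table shows how often.

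**Conclusion.** The point holds in a limited form: the article credits a non-significant result with a meaning that the design does not support. Power for a true 20-point gain is 50 to 60% at 39 per arm and 38 to 50% at 31 per arm, and 80% power needs about 26 to 30 points with the z test. Three assumptions matter. The sham rate is the article's 10.83%; a higher rate would lower the power for the same absolute gains. The 15- and 20-point gains are illustrations, since the documents set no worthwhile difference. The test is unadjusted; the article does not fix the regression model or its covariates. The weakness affects what may be concluded, not the endpoint, the sample size or the conduct of the trial.

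**What to change.** Under Potential impact and clinical implications, replace the sentence on a non-significant result. Say that a null will be read from the 95% confidence interval for the risk difference in discontinuation at week 6. State in advance the smallest difference regarded as worthwhile, with the reason for it. Conclude that there is no worthwhile benefit only if the upper limit lies below that difference; otherwise call the result inconclusive.

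This does not make every null uninformative. At 4/39 in both arms the Newcombe interval is about -15 to +15 points, which would exclude a benefit of 20 points.

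The cost is a few sentences and one clinical judgement, made before the data are seen. The sample size is unchanged. The downside is that many null results would support a weaker statement than the article now promises.
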